# **Effect of More versus Less Frequent Follow-Up Testing on 10-Year Overall and Colorectal Cancer-Specific Mortality in Patients with Stage II or III Colorectal Cancer: a Post-trial Analysis of the COLOFOL Trial**

## **Statistical Analysis Plan**

### ***1) Study design***

The COLOFOL study group was established in 2004. Twenty-four recruitment centers in Denmark, Sweden, and Uruguay contributed patients to the trial. The objective of this prospective multicenter randomized trial was to examine overall and colorectal cancer-specific mortality rates in patients with Stage II or Stage III colorectal cancer who were randomized after undergoing curative surgery to 2 groups with alternative schedules for follow-up testing with computerized tomography (CT) scans and carcinoembryonic antigen (CEA) testing.

All centers participating in the COLOFOL trial were required by the protocol to follow up on all study participants with surveillance examinations until 3 years post-surgery and to report outcomes to the study's coordinating center until 5 years after surgery.

Although the trial did not yield entirely conclusive results, the findings revealed a small but potentially important clinical difference between the 2 groups.

This post-trial follow-up study aims to conduct a follow-up analysis of the patients included in the COLOFOL study in Denmark and Sweden that extends beyond the initial 5 years of follow-up.

### ***2) Principles of analysis***

Results will be evaluated both on an intention-to-treat and an as-treated (per-protocol) basis. Patients who withdrew their informed consent and thus changed their follow-up regimen will remain in their allocation groups for the intention-to-treat analysis but will be excluded from the per-protocol analysis.

Patients who incurred a protocol violation during the study period (including participation in other clinical trials that interfered with the follow-up regimen), who developed a new primary cancer, or whose records are missing data on key variables will also be excluded from the per-protocol analysis.

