## **Statistical analysis and power**

Results will be evaluated both on an intention-to-treat basis and on an as-treated (per protocol) basis. Patients who withdraw their informed consent and, thus, change their control-programme remain in their allocation group when evaluated on the intention-to-treat basis, and are excluded when evaluated on the fulfilled protocol basis. Non-randomised patients and patients withdrawing their informed consent will be analysed separately.

On the basis of the results listed in Figure 1, an estimate of 5 years' mortality at 60% and a MIREDF (Minimal Relevant Difference) of 6% seem justified. With a risk of type 1 error at 5% and type 2 error of 15%, about 1,100 patients should be randomised to each group. With an expected dropout rate of about 20%, the planned number of randomised patients should be 2,500.

Survival data will be analysed according to the Kaplan-Meier method and comparison between groups will be performed with the log-rank method. Binominal data will be analysed with Chi-square statistics and continuous data with Mann-Whitney U test.

No interim analyses are planned, as this would stop inclusion for several years.

Level of significance two-sided  $p < 0.05$ .

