| Outcome                                                               |                                  |                                       |
| Recurrence of colorectal cancer denied:                                      |  ▼ |                                       |
| Recurrence of colorectal cancer suspected:                                   |  ▼ |                                       |
| Recurrence of colorectal cancer operable:                                    |  ▼ |                                       |
| Location of metastasis:                                                      |  ▼ |                                       |
| Recurrence of colorectal cancer confirmed:                                   |  ▼ |                                       |
| - How many:                                                                  |              |                                       |

|                                       |                                     |                                       |
|---------------------------------------|-------------------------------------|---------------------------------------|
| - Size of the largest (maximum):      |                 | mm                                    |
| Metachronous cancer determined:       |       |       |
| Blood samples                  |                                     |                                       |
| Blood samples to biological bank:     |       |       |
| Tissue samples to bio bank:           |       |       |
|  |  |  |

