#### *Low-frequency follow-up regimen*

- CEA screening preoperatively and 1 month postoperatively. Missing preoperative CEA results will not be considered an exclusion criterion and will be handled as missing data.
- CEA screening, multi-slice CT or magnetic resonance imaging (MRI) of the liver, and X-ray/CT of the lungs at 12 and 36 months post-surgery. Patients were instructed to contact their recruitment center if they experienced any symptoms of disease recurrence.
- If recurrent disease is suspected, participants will undergo a standard work-up for diagnosis and treatment.

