#### *High-frequency follow-up regimen*

- CEA screening preoperatively and 1 month postoperatively. Missing preoperative CEA results will not be considered an exclusion criterion and will be handled as missing data.
- CEA screening, multi-slice hepatic CT or MRI of the liver, and X-ray or CT of the lungs at 6, 12, 18, 24, and 36 months post-surgery. Patients were instructed to contact their recruitment center if they experienced any symptoms of disease recurrence.
- If recurrent disease is suspected, participants will undergo a standardized work-up for diagnosis and treatment (see Appendices 2–3).

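### The 10-year per-protocol set drops patients who later develop a new primary cancer; this post-randomisation exclusion can bias the comparison, in an unknown direction

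*Combined protocol and SAP*

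**What the plan says.** The post-trial SAP, section 2, plans two evaluations: "Results will be evaluated both on an intention-to-treat and an as-treated (per-protocol) basis". Neither is called primary. Consent withdrawals leave the per-protocol set, and so do several further groups. The sentence opens with "Patients who incurred a protocol violation during the study period" and goes on to those "who developed a new primary cancer, or whose records are missing data on key variables will also be excluded from the per-protocol analysis". It does not say whether the study period also limits the new-primary clause, whether that period means 3, 5 or 10 years, which source identifies a new primary, or which variables are key.

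Other relevant provisions:

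- **Schedules (SAP section 3).** Low frequency has liver imaging, CEA and "X-ray/CT of the lungs at 12 and 36 months post-surgery". High frequency has the same tests with "X-ray or CT of the lungs at 6, 12, 18, 24, and 36 months post-surgery". Both regimens say that a missing preoperative CEA is not a ground for exclusion and is handled as missing data.
- **Duration (SAP section 1).** Centres were to carry out "surveillance examinations until 3 years post-surgery".
- **Follow-up and methods (SAP section 6).** Time runs from radical surgery. Deaths from other causes are competing events for colorectal cancer-specific mortality.
- **Protocol, Statistical analysis and power.** Patients who withdraw consent "are excluded when evaluated on the fulfilled protocol basis". No other ground is named there.
- **Follow-up form, Outcome block.** One field reads "Metachronous cancer determined", so a new cancer can be recorded at a study visit.

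**The concern.** A per-protocol set is meant to show what happens when the assigned regimen is followed. A patient who attends every scheduled test and then develops another cancer has followed it. Excluding that patient selects on a later outcome, and only those who live long enough to be diagnosed can be selected. Since the clock starts at surgery, they vanish from the risk set from day one.

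The selection need not be equal between arms. The high-frequency arm has three more imaging rounds (6, 18 and 24 months), hence more scheduled occasions to find or record another cancer. For overall mortality, a death from a new primary is an endpoint event, and the rule discards it. For colorectal cancer-specific mortality, the competing-event method already deals with such a death.

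The clause on missing key variables adds selection that also has nothing to do with adherence. Because the term is undefined, it could catch patients whose missing preoperative CEA section 3 says is not a reason for exclusion.

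The SAP calls the trial's earlier difference between arms small but potentially important. A selection effect of a point or so in a result shown beside intention-to-treat could affect how the 10-year findings are read.

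**Working it through.** The documents state no figure for the per-protocol set, so there is nothing to reproduce. **All rates below are assumptions**, chosen to show how the rule behaves when the true effect is zero.

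**Formula.** With arm mortality m, share excluded q, and mortality mq among those excluded, per-protocol mortality is (m - q x mq) / (1 - q). Differences are high minus low, so negative favours high frequency.

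**Overall mortality, m = 38% in both arms**

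1. Low 8% and high 12% excluded, 60% mortality among them:
   - Low: (0.38 - 0.08 x 0.60) / 0.92 = 0.332 / 0.92 = 36.1%
   - High: (0.38 - 0.12 x 0.60) / 0.88 = 0.308 / 0.88 = 35.0%
   - Difference: -1.1 points. Deaths removed per 100 patients: 4.8 (low) and 7.2 (high), out of 38.
2. Same shares, 70% mortality among those excluded:
   - Low: 0.324 / 0.92 = 35.2%. High: 0.296 / 0.88 = 33.6%
   - Difference: -1.6 points.
3. Common 8% at 60% mortality, but the extra 4% in the high arm at 20% (indolent or early-found cancers):
   - High: (0.38 - 0.048 - 0.008) / 0.88 = 0.324 / 0.88 = 36.8%, against 36.1% in the low arm
   - Difference: +0.7 points.
4. Equal shares with equal mortality, for example 10% against 10%: difference 0.

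**Where the sign turns.** If the high arm excludes an extra share d with mortality mx on top of a common share q, and r is the mortality of those retained in the low arm, the formula reduces to d x (r - mx) / (1 - q - d). With r = 36.1%, q = 8% and d = 4%:

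- mx = 60%: 0.04 x (0.361 - 0.60) / 0.88 = -1.1 points
- mx = 20%: 0.04 x (0.361 - 0.20) / 0.88 = +0.7 points
- mx = 36.1%: 0

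**Colorectal cancer-specific mortality.** Assume 20% overall and 5% among those excluded, since many would die of the other cancer, with 8% and 12% excluded:

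- Low: (0.20 - 0.004) / 0.92 = 21.3%
- High: (0.20 - 0.006) / 0.88 = 22.0%
- Difference: +0.7 points, against the high arm.

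**Sensitivity to the inputs.** Other assumed values go outside the span -1.6 to +0.7:

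- At 30% mortality, with a common 8% excluded at 70% mortality and an extra 3% in the high arm at 80%: 0.220 / 0.89 - 0.244 / 0.92 = 24.7% - 26.5% = -1.8 points.
- At 30% mortality, with 10% excluded in both arms at 50% mortality (high) and 70% (low): 0.250 / 0.90 - 0.230 / 0.90 = 27.8% - 25.6% = +2.2 points.

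The span is therefore an illustration, not a bound.

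**The case against.** The best defence is that the damage is limited. Intention-to-treat is planned alongside and is untouched by the rule, so deaths from new primaries are not lost to the study. Scheduled imaging ends at 3 years in both arms, chest imaging may be plain X-ray in either, and the protocol wants endoscopy on the same schedule in both arms. If the follow-up form's field refers to second colorectal cancers, differential detection is weaker still. The SAP takes outcomes from population registries. If new primaries were identified there over the full 10 years, many low-arm cancers would surface and be excluded too. All of this stands as mitigation. However, section 4 ties the registries to outcomes, and section 2 gives neither source nor window for this exclusion.

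A reader might infer that the rule favours high frequency and manufactures a mortality benefit. The documents do not support that. It needs both more exclusions in the high arm and, among the extra cases, higher mortality than in the patients retained. Neither is documented, and the sign reverses under other plausible inputs.

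A reader might also infer that the 5-year per-protocol set excluded consent withdrawals and nobody else. The protocol names withdrawals but does not say they are the only ground, and the 10-year population differs anyway because Uruguay is left out.

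**Conclusion.** The exclusion is wrong as written: it removes patients from time zero for a later health event that is not non-adherence and whose detection may depend on arm. What can be said is that it may bias the 10-year per-protocol comparison, with direction and size unknown. In the 38% illustration the shift in overall mortality is about -1.6 to +0.7 points, while colorectal cancer-specific mortality may move about 0.7 points against the high arm. The two endpoints can thus be pushed in opposite directions. These sizes rest wholly on assumed incidence and mortality of new primaries, and the shift is zero when equal shares with equal mortality are excluded.

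The main safeguard is intention-to-treat, but the SAP does not give it priority. The point is worth correcting before analysis; it does not undermine the study.

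**What to change.** In section 2 of the post-trial SAP:

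- Delete the new-primary exclusion. Keep these patients in follow-up, count their deaths as events for overall mortality, and count deaths from the new cancer as competing events for colorectal cancer-specific mortality, as section 6 already provides.
- Delete the missing-key-variables exclusion. Handle missing covariates, by exclusion or imputation, only in the adjusted Cox model, in line with section 3 on missing preoperative CEA.
- Name intention-to-treat as primary.
- Report per-protocol exclusions by arm and reason.
- If the sponsor wants a version without new primaries, show it only as a labelled sensitivity analysis, with the time window and data source for new primaries defined.

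Redefining per-protocol purely by completion of the assigned tests is not advised as a replacement. Patients who recur, fall ill or die miss tests, and the high arm has more tests to miss, so that rule brings its own post-randomisation selection.

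The cost is revised SAP wording, a changed analysis-set flag and a slightly larger per-protocol set. No new data are needed.

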### 3) *Exposure variables*

Trial participants' data will be analyzed according to the group to which they were randomly assigned:

#### *Low-frequency follow-up regimen*

- CEA screening preoperatively and 1 month postoperatively. Missing preoperative CEA results will not be considered an exclusion criterion and will be handled as missing data.
- CEA screening, multi-slice CT or magnetic resonance imaging (MRI) of the liver, and X-ray/CT of the lungs at 12 and 36 months post-surgery. Patients were instructed to contact their recruitment center if they experienced any symptoms of disease recurrence.
- If recurrent disease is suspected, participants will undergo a standard work-up for diagnosis and treatment.

#### *High-frequency follow-up regimen*

- CEA screening preoperatively and 1 month postoperatively. Missing preoperative CEA results will not be considered an exclusion criterion and will be handled as missing data.
- CEA screening, multi-slice hepatic CT or MRI of the liver, and X-ray or CT of the lungs at 6, 12, 18, 24, and 36 months post-surgery. Patients were instructed to contact their recruitment center if they experienced any symptoms of disease recurrence.
- If recurrent disease is suspected, participants will undergo a standardized work-up for diagnosis and treatment (see Appendices 2–3).

### 4) *Endpoints*

The following endpoints will be analyzed:

- 10-year overall mortality rates and
- 10-year colorectal cancer-specific mortality rates.

The outcomes will be obtained from population-based cancer, death, pathology, and patient registries in Denmark and Sweden. We will exclude patients from Uruguay because we are unable to obtain adequate follow-up information from these patients.

### **5) *Analysis of baseline data***

Trial participants will be described according to the group to which they were randomly assigned and by categories of baseline characteristics. Categorical data will be presented as counts and percentages, and continuous data will be presented as medians and interquartile ranges.

### **6) *Analysis of follow-up data***

Trial participants will be followed from the date of radical surgery for colorectal cancer until the date of the analyzed study outcome, date of dropout, date when lost to follow-up, or at 10-year follow-up, whichever comes first.

The Kaplan-Meier method and the log-rank test for between-group comparisons will be used to analyze 10-year overall mortality in the post-trial group participants. The colorectal cancer-specific mortality rates will be calculated using a cumulative incidence function and treating death associated with other causes as competing events. Risk differences in the 10-year overall and colorectal cancer-specific mortality will be calculated with corresponding 95% confidence intervals.

The main analyses will be stratified by cancer stage and will be repeated for the subgroups of patients diagnosed with rectal and colon cancer.

In the first sensitivity analysis, we will repeat the main analyses for trial participants from Denmark and Sweden. The overall and colorectal cancer-specific mortality rates will be compared between the 2 countries.

In a second sensitivity analysis, Cox proportional hazards regression will be used to compute crude and adjusted hazard ratios for overall and colorectal cancer-specific mortality rates. The hazard ratios will be adjusted for age at the time of colorectal cancer surgery; sex; colorectal cancer type; cancer stage; comorbidities including diabetes, cardiovascular disease, pulmonary disease, and cerebrovascular disease; preoperative radiation; adjuvant chemotherapy; and smoking.

The level of significance will be  $P < .05$  with a 2-sided test. Statistical software package SAS (SAS Institute, Inc., Cary, NC, USA) will be used for data management and analyses.

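### The 10-year SAP ends follow-up at an undefined dropout date, even in the intention-to-treat analysis, so deaths obtainable from the registries may be discarded

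*Combined protocol and SAP*

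**What the plan says.** All references are to the 10-year post-trial SAP unless stated otherwise.

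- **Section 6 (Analysis of follow-up data)** starts follow-up at surgery and runs it "until the date of the analyzed study outcome, date of dropout, date when lost to follow-up, or at 10-year follow-up, whichever comes first". The rule is stated once, for all participants and both endpoints, with no separate version for the intention-to-treat (ITT) analysis. The same section says: "The Kaplan-Meier method and the log-rank test for between-group comparisons will be used to analyze 10-year overall mortality". Cancer-specific mortality uses a cumulative incidence function with other deaths as competing events.
- **Section 2 (Principles of analysis)** describes one kind of leaver: "Patients who withdrew their informed consent and thus changed their follow-up regimen". These patients "will remain in their allocation groups for the intention-to-treat analysis but will be excluded from the per-protocol analysis".
- **Section 4 (Endpoints)**: "The outcomes will be obtained from population-based cancer, death, pathology, and patient registries in Denmark and Sweden". It adds: "We will exclude patients from Uruguay because we are unable to obtain adequate follow-up information from these patients".
- **Section 1 (Study design)** has centres carry out surveillance for 3 years and obliges them "to report outcomes to the study's coordinating center until 5 years after surgery".

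No section defines dropout or says whether withdrawing consent also withdraws permission to use registry data.

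**The concern.** Because dropout is listed next to loss to follow-up, it must cover some patients whose status could still be known. The only description of leaving in this SAP ties it to a change of follow-up regimen. On that reading, a patient who stops attending at year 2 is kept in the assigned arm but contributes nothing from year 2 to year 10, although a death in year 6 would be in the national register.

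Two things are at stake. Events that could be obtained are lost. And Kaplan-Meier, the log-rank test, the cumulative incidence function and the Cox model all treat censored patients as having the same later risk as those still followed. Patients know their schedule, and the schedules differ in burden (section 3: two post-baseline test rounds against five), so leaving could be related to prognosis and could differ by arm. Neither planned sensitivity analysis (by country; Cox regression) addresses this.

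**Working it through.** **Step 1. The text.** Section 2 fixes the group in which a patient is analysed. Section 6 fixes how long that patient is observed. Both can be followed at once: the patient stays in the arm and is censored at dropout. What results is ITT in group membership but not in follow-up. Sections 1 and 4 show that the censoring is not forced by the data source. Centre reporting stops at 5 years, so for years 5 to 10 nobody's outcome depends on staying in the programme, and the country without adequate follow-up is already excluded.

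**Step 2. Figures available.** The 10-year SAP states no dropout rate, event count or sample size, so there is no figure to reproduce. Everything below is illustration. Inputs from the original trial's sample-size paragraph: 60% 5-year mortality, a 6-point difference, about 20% dropout, 2,500 patients. Assumptions of this review: constant hazard, dropout times uniform over years 0-3, dropout of 5% or 10% as alternatives, and 25% 5-year mortality as a lower scenario.

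**Step 3. Deaths lost.** With hazard λ = −ln(1 − m)/5, where m is 5-year mortality, and a share d who would drop out:

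- lost = d × [(1 − e^(−3λ))/(3λ) − e^(−10λ)]
- all deaths by 10 years = 1 − e^(−10λ)

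For m = 60%, λ = 0.1833. At d = 20%, lost = 0.20 × (0.769 − 0.160) = 0.122, out of 0.840, or 14.5%. For m = 25%, λ = 0.0575. Lost = 0.20 × (0.918 − 0.5625) = 0.071, out of 0.4375, or 16.3%.

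| Dropout | Share of deaths lost, m = 60% | Share of deaths lost, m = 25% |
|---|---|---|
| 5% | 3.6% | 4.1% |
| 10% | 7.3% | 8.1% |
| 20% | 14.5% | 16.3% |

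A second model lets risk vary between patients (gamma(1,1) frailty, base hazard 0.075 per year, 10-year mortality about 43%). When patients of above-median risk are 1.5 to 3 times as likely to drop out, it gives 17-19% lost at 20% dropout and about 4-5% at 5%. Spreading dropout over years 0-5 in the constant-hazard model lowers the 20% figures to 11.8% (m = 60%) and 14.0% (m = 25%).

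**Step 4. Precision.** With 2,500 patients and 60% against 54% at 5 years, HR = ln(0.46)/ln(0.40) = 0.847. Power = Φ(√(events/4) × |ln HR| − 1.96). Without dropout there are 2,036 events and power is 96.2%. With 20% dropout there are 1,736 events and power is 93.2%.

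**Step 5. Bias in one arm.** Let would-be dropouts have k times the hazard λ of the others, and let G(t) = 1 − t/3 up to year 3 and 0 afterwards.

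- true 10-year mortality = 1 − d e^(−10kλ) − (1 − d) e^(−10λ)
- Kaplan-Meier tends to 1 − exp(−∫h), with h(t) = [d G kλ e^(−kλt) + (1 − d) λ e^(−λt)] / [d G e^(−kλt) + (1 − d) e^(−λt)]

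Example with λ from m = 25%, d = 20%, k = 0.5: truth = 1 − 0.2 × 0.75 − 0.8 × 0.5625 = 40.0%, Kaplan-Meier 43.2%, bias +3.2 points. Results at 20% dropout:

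| λ from | k = 0.5 | k = 1 | k = 1.5 | k = 2 |
|---|---|---|---|---|
| m = 60% | +4.3 | 0 | −1.5 | −1.9 |
| m = 25% | +3.2 | 0 | −2.3 | −3.9 |

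At 5% dropout the range is +1.1 to −0.5 points (m = 60%) and +0.8 to −1.0 (m = 25%).

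**Step 6. Bias in the risk difference.** If both arms share the same dropout pattern and there is no true effect, the arm biases cancel. In the frailty model with no true effect, 20% dropout in one arm against 10% in the other, and higher-risk patients 1.5 to 3 times as likely to leave, the spurious difference is about 0.5 to 1.3 points.

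**The case against.** The strongest reply is that dropout may mean withdrawal of consent to any further use of data. The protocol's ethics section allows consent to be withdrawn at any time, and no section says that registry linkage survives this. For such patients censoring at withdrawal may be unavoidable. That stands, and it is why the point is conditional. But the SAP does not say that this is what dropout means, and its own description of leaving concerns a change of regimen.

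The second reply is that the effect may be small. The 20% was an expectation for the original sample size, not an observed rate or one for this cohort. It does not even match its own inflation: 1 − 2,200/2,500 = 12%. The power loss in step 4 is modest, and bias needs dropout to be related to prognosis. All of this stands as a limit on the size, not as a reason to keep the rule.

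A reader might infer more than the documents support:

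- *That section 6 contradicts section 2.* It does not. Section 2 governs group membership and is silent on length of follow-up.
- *That mortality will be understated, or that one arm will be favoured.* No section says who leaves or how many leave in each arm. A difference in test burden makes unequal dropout possible, not established.
- *That starting the clock at surgery is part of the same problem.* The original SAP places consent within 30 days of surgery, and the protocol recommends an allocation visit at 4-6 weeks. The interval is short and common to both randomised arms.

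**Conclusion.** The concern holds in a conditional form. As written, the rule censors the ITT analysis at an undefined dropout date although outcomes come from registries that do not depend on staying in the programme. For patients who left only the surveillance schedule, this discards obtainable deaths and makes both endpoints rest on an untested assumption that leaving is unrelated to prognosis.

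The size cannot be fixed from the documents. Under the stated assumptions, roughly 4-5% of 10-year deaths are lost at 5% dropout and 15-19% at 20%, somewhat fewer if dropout comes later. Bias in an arm's 10-year mortality is zero under unrelated dropout, about a point at most at 5% dropout, and up to about 4 points in either direction at 20%. The risk difference is affected only if the dropout pattern differs by arm. Section 1 describes the trial's observed difference as small, so even a spurious difference of about a point would matter to the reading. The rule should be settled before the analysis.

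**What to change.** 1. Define dropout, separating leaving the follow-up regimen from refusing use of registry data.
2. In the ITT analysis, follow every randomised Danish and Swedish patient through the registries to death, emigration or 10 years, whichever is first, regardless of adherence to the regimen.
3. Censor at withdrawal only where use of registry data was also refused, and report the number and timing of these patients by arm.
4. Confine any other censoring at dropout to the per-protocol analysis.

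The cost is a change of SAP wording and one change to the derivation of follow-up time. The registry data are already planned for. The real work is checking what each consent withdrawal covers, and some patients may still have to be censored.
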